### Secondary outcome measures

#### Length of postoperative hospital stay

The length of postoperative hospital stay is an important index used to determine the clinical effect of treatment, which is relatively objective and intuitive (24–26).

#### Intensity of postoperative abdominal pain and distension

The abdominal pain will be assessed by the visual analog scale (VAS), which has been proven less vulnerable to confounding factors and ceiling effects than other pain scales (27–29). The intensity of abdominal distension can be divided into four grades: no symptoms, mild, moderate, and severe. Both indexes will be obtained 1 day after surgery and at the time of discharge.

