**Figure 1 F1:**
[figure not shown]
Flowchart of research.

**Table 1 T1:** Details of the study period.

	Study period				
	Visit 1	Visit 2	Visit 3	Visit 4	Visit 5
Time node	−7 to 0 day	0 day	3 days before surgery	Day 1–3 after surgery	Discharged from the hospital
Enrollment					
Informed consent	●				
General information	●				
Medical history	●				
Randomization		●			
Intervention					
AA + MA					
ERAS					
Assessment					
First defecation				●	
First flatus				●	
Length of postoperative hospital stay					●
Intensity of abdominal pain and distension				●	●
Severity of PNOV				●	●
Time to tolerate diet				●	●
Inflammatory index		●		●	●
Incidence of PPOI					●
Safety observation			●	●	●
Adverse event record			●	●	●
Obedience evaluation					●

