## Interventions

### Intervention group: MA combined with AA

MA and auricular acupressure procedures of the intervention group will be administered by licensed acupuncturists with 5–12 years of education in acupuncture and at least 3 years of clinical experience. They will all undergo unified and standardized training before trial initiation.

The intervention group will accept AA at the small intestine (CO6), large intestine (CO7), abdomen (AH8), and sub-cortex (AT4) according to the *Nomenclature and Location of Auricular Points* (Table 2 and Figure 2). Vaccaria seeds (Wang-Bu-Liu-Xing) (40 mm × 40 mm) (Changshu Shenling Medical Products Factory Co., Ltd., Changshu, China) will be embedded on the surface of auricular points and maintained between the two treatments. Two ears will accept AA alternately once daily. Participants will be suggested to press each point gently for 1 min thrice daily. The treatment will start 3 days before elective laparoscopic surgery and continue until the first defecation after surgery.

**Table 2 T2:** Location of auricular acupoints.

Auricular acupoints	Locations
Small intestine (CO6)	At the intermediate 1/3 of the region between the helix crus and Line AB^a^
Large intestine (CO7)	At the anterior 1/3 of the region between the helix crus and Line AB
Abdomen (AH8)	On the upper 2/5 of the body of the antihelix crus
Sub-cortex (AT4)	On the medial side of the antitragus

Point A: At the medial edge of the helix at the junction between the middle and upper 1/3 of the line from the notch of the helix crus and the inferior edge of the inferior antihelix crus. Point B: At the junction of the middle and posterior 1/3 of the line extending from the end of the helix crus to Point D. Point D: At a level line drawn from the end of the helix crus crossing the concha edge of the antihelix.

^a^
Line AB: A curved line that extends from Point A to Point B and mirrors the inferior edge of the helix crus.

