**Figure 2 F2:**
[figure not shown]
Location of auricular acupoints.

The intervention group will also accept MA at *Zusanli* (ST36), *Shangjuxu* (ST37), *Xiajuxu* (ST39), *Hegu* (LI4), and *Taichong* (LR3) according to *Acupuncture and Moxibustion* (23) (Table 3 and Figure 3). A single-use stainless steel needle (0.25 mm × 40 mm) (Suzhou Medical Products Factory Co., Ltd., Suzhou, China) will be used, and Deqi sensation (a sensation of sourness, numbness, or distension) should be achieved during the process. The needle should be retained for 20 min and then withdrawn quickly. Patients will receive MA once a day for consecutive days after surgery until the first defecation after surgery.

**Table 3 T3:** Location of acupoints.

Acupoints	Locations
Zusanli (ST36)	On the lateral aspect of the leg, 3 cun inferior to Dubi (ST35), on the line connecting Dubi^a^ (ST35) and Jiexi^b^ (ST41)
Shangjuxu (ST37)	On the lateral aspect of the leg, 6 cun inferior to Dubi (ST35), on the line connecting Dubi(ST35) and Jiexi(ST41)
Xiajuxu (ST39)	On the lateral aspect of the leg, 9 cun inferior to Dubi (ST35), on the line connecting Dubi (ST35) and Jiexi (ST41)
Hegu (LI4)	On the dorsum of the hand, radial to the midpoint of the second metacarpal bone
Taichong (LR3)	On the dorsum of the foot, between the first and second metatarsal bones, in the depression anterior to the junction of the bases of the two bones, or over the dorsalis pedis artery

^a^
Dubi (ST35): On the anterior aspect of the knee, in the depression lateral to the patellar ligament.

^b^
Jiexi (ST41): On the anterior region of the ankle, in the depression at the center of the front surface of the ankle, between the extensor halluces longus tendon and the extensor digitorum longus tendon.

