#### Inflammatory index

The inflammatory index includes white blood cell (WBC) count and the levels of C-reactive protein (CRP), interleukin-6 (IL-6), procalcitonin (PCT), and tumor necrosis factor-α (TNF-α), which will be obtained at baseline, 1 day after surgery, and at the time of discharge.

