## Statistical analysis

The principle of intention-to-treat (ITT) analysis will be followed in the process of statistical analysis. The last observation carried forward (LOCF) analysis will be applied for missing data in ITT analysis. Supplementary per-protocol analysis will also be carried out. All the statistical analyses will be performed using SPSS Ver. 24.0 with a significance level of 0.05.

First, the different baseline characteristics of the two groups will be described, and data will be presented as mean or median with standard deviation or interquartile range for continuous variables and as frequency distributions for categorical variables. Moreover, the histograms, boxes, and other representations will also be considered for the graphic analysis of corresponding data. A two-sample *t*-test for quantitative data or a chi-squared test for qualitative data will be performed as a homogeneity test, and the covariance analysis will also be performed if an adjustment is needed for a baseline characteristic.

Second, the analyses will focus on whether statistically better treatment outcomes could be achieved in the intervention group. *P*-values less than 0.05 will be considered statistically significant, and tests will be two-sided.

In terms of the changes in the measurement data, the two-sample *t*-test or the Wilcoxon rank-sum test will be used to compare the two groups and to determine differences according to normality. The mean change and the interaction between groups and observed time frames will be analyzed using a two-factor repeated measure analysis. If necessary, a mixed model approach will also be used.

Finally, safety analysis will be performed using the chi-squared test or Fisher's exact test based on the frequency and percentage of all recorded adverse events between the two groups.

The above plan is what we intend to do; however, the final analyses reported may differ from those planned, allowing for *post-hoc* analysis where it is indicated.

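### VAS abdominal pain is measured only after treatment has begun, so the change and group-by-time interaction named in the analysis plan do not estimate the treatment effect on pain

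*Protocol article*

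**What the plan says.** All references are to the protocol article.

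- **When pain is measured.** The section on intensity of postoperative abdominal pain and distension states "Both indexes will be obtained 1 day after surgery and at the time of discharge". In Table 1 the row "Intensity of abdominal pain and distension" carries two marks, which read as Visit 4 (days 1–3 after surgery) and Visit 5 (discharge).
- **When treatment runs.** For auricular acupressure, the intervention section states "The treatment will start 3 days before elective laparoscopic surgery and continue until the first defecation after surgery". For manual acupuncture: "Patients will receive MA once a day for consecutive days after surgery until the first defecation after surgery".
- **What is analysed.** The between-group part of the Statistical analysis section begins "In terms of the changes in the measurement data, the two-sample" and goes on to the t-test or, depending on normality, the Wilcoxon rank-sum test. It continues: "The mean change and the interaction between groups and observed time frames will be analyzed using a two-factor repeated measure analysis". A mixed model is held in reserve. No outcome is named and none is exempted.
- **The contrast case.** The inflammatory markers have a pre-treatment sample, "which will be obtained at baseline, 1 day after surgery, and at the time of discharge".

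**The concern.** A change score or a group-by-time interaction measures benefit when the first value precedes treatment, because randomisation then makes the arms alike at that point in expectation. The inflammatory index fits this pattern. VAS pain does not: its first value comes about four days after acupressure begins (three days before surgery plus one day after), so any early benefit is already in the starting value. A patient whose day-1 pain was lowered by treatment has less room to improve by discharge.

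Fading of a benefit by discharge is plausible. Both treatments stop at first defecation, and symptoms may well be mild by the time a patient goes home (the latter is my inference). Discharge also occurs at a patient-specific time that treatment may shift, since length of postoperative stay is itself an outcome. Symptom relief is part of the stated aim, so the wrong contrast could lead the report to miss or misread an effect on pain.

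**Working it through.** **The plan's own figure.** The only sample size stated is for time to first defecation; none is given for pain. With a difference of 85.1 − 77.8 = 7.3 h, SD 15.6 h in both arms, two-sided 0.05 and power 0.80:

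n = 2 × (1.960 + 0.842)² × 15.6² / 7.3² ≈ 71.7, so 72 per group; 72 / 0.9 = 80.

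This reproduces the plan. It is used below only for the number of evaluable patients per group.

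**What the named contrasts estimate.** Let control means be m1 (day 1) and m2 (discharge), and let the intervention lower pain by b1 and b2 at those times.

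- Mean change, control: m2 − m1.
- Mean change, intervention: (m2 − b2) − (m1 − b1).
- Difference in change, intervention minus control: b1 − b2.

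With two times, the interaction in a two-factor model is the same quantity. In effect terms (effect = −b) it is the effect at discharge minus the effect on day 1.

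- Constant benefit (b1 = b2): zero.
- Fading benefit (b1 > b2): positive, so pain falls less in the intervention arm and the change score favours control.
- Benefit growing by discharge (b2 > b1): the change favours the intervention, but still misses the part already present on day 1.

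This algebra needs no assumed figures.

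**Illustrative size.** Assumptions, none from the documents: b1 = 0.5 SD, equal SDs at both times, within-patient correlation ρ from 0.2 to 0.7. Noncentral t, 72 per group, two-sided 0.05.

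- Direct comparison of day-1 scores: d = 0.5, power 84.6%.
- Change score: d = (b1 − b2) / √(2(1 − ρ)), with b in SD units.
- Group main effect (mean of the two scores): d = ((b1 + b2)/2) / √((1 + ρ)/2).

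| ρ | Constant: change test rejects | Halved: change significant for control | Gone: change significant for control | Constant: main-effect power | Gone: main-effect power |
|---|---|---|---|---|---|
| 0.2 | 5% | 21.7% | 65.4% | 97.0% | 48.5% |
| 0.3 | 5% | 24.2% | 71.2% | 95.9% | 45.5% |
| 0.5 | 5% | 31.9% | 84.6% | 93.1% | 40.5% |
| 0.7 | 5% | 48.5% | 97.0% | 89.8% | 36.5% |

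A separate simulation (4,000 runs, VAS SD 2, day-1 benefit 1 point, ρ = 0.3, 0.5, 0.7) agrees. Day-1 power was about 84–85%. Under a constant benefit the change test favoured the intervention in 2.2–2.5% of runs. It favoured control in 24%, 32% and 49% of runs with a halved benefit, and in 71%, 84% and 97% with a vanished one.

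**The case against.** The strongest reply is that the analysis section never assigns the change analysis to pain. Its wording is generic, the inflammatory markers fit it fully, and mapping tests to secondary outcomes is commonly left to a fuller document that is not shown. This narrows the point but does not remove it. The complaint is not about missing detail: the section positively names change and interaction as contrasts, VAS pain is a measured quantity recorded twice, and nothing excludes it.

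Two further objections stand and limit the claim.

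- **The same model also yields a group main effect.** It keeps a constant benefit, with roughly 90–97% power in the illustration. A reader might infer that the planned model as a whole is blind to a constant benefit; it is not. But the text names the mean change and the interaction, not the group effect.
- **An interaction does not name a winner.** It says only that the arms' profiles differ. With a fading benefit, the arm means would show the intervention lower on day 1. The wrong-direction percentages apply to a change score read without those means.

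Two stronger readings are tempting but unsupported.

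- **That the missing preoperative score is itself an error.** These are postoperative symptoms. Randomisation makes a direct comparison at each time valid and balances pre-existing pain in expectation.
- **That the fault extends equally to distension and nausea and vomiting.** For distension, "The intensity of abdominal distension can be divided into four grades: no symptoms, mild, moderate, and severe", so it may be handled as qualitative data. The nausea and vomiting scale comes with a cut-off that points at least partly to incidence.

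**Conclusion.** The point holds for VAS pain. On the stated schedule, the change and the interaction estimate the effect at discharge minus the effect on day 1, not the benefit of treatment. That follows from the measurement times alone. Table 1's wider window for Visit 4 does not alter it, since any day in that window is after treatment has started.

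The size is less certain. The power and wrong-direction figures rest on an assumed 0.5 SD benefit, equal SDs and assumed correlations; the largest also need the benefit to vanish completely by discharge. They show what can happen, not what will. For distension and for nausea and vomiting, the point applies only if they are analysed as scores. The impact is confined to secondary outcomes; the primary outcomes and the sample size are untouched.

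**What to change.** Add one sentence to the Statistical analysis section. For VAS pain, and for distension and nausea and vomiting if analysed as scores:

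- the effect analysis is the between-group comparison of the day-1 score;
- the discharge score or the group main effect is supporting;
- the day-1-to-discharge change and the group-by-time interaction are not used as evidence of benefit.

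Keep the change-from-baseline analysis for the inflammatory index, which has the baseline sample it needs.

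The cost is close to nil. No new data are required, patients already enrolled lose nothing, and the article reports that recruitment is still under way, so the change can be made before analysis. A preoperative pain score used as a covariate could add precision, but it is optional and would be unavailable for patients already enrolled.

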#### Severity of postoperative nausea and vomiting

The simplified postoperative nausea and vomiting (PONV) impact scale, which consists of two questions, will be used to evaluate postoperative nausea and vomiting (30). Clinical PONV can be defined when the impact scale score is more than 5.

#### Time to tolerate diet (liquid or semi-liquid food)

Postoperative ileus can result in delays in time to mobilization and resumption of oral intake, which may further affect patient's satisfaction and wound recovery (31). Therefore, the time to tolerate diet will be recorded as a reference.

#### Inflammatory index

The inflammatory index includes white blood cell (WBC) count and the levels of C-reactive protein (CRP), interleukin-6 (IL-6), procalcitonin (PCT), and tumor necrosis factor-α (TNF-α), which will be obtained at baseline, 1 day after surgery, and at the time of discharge.

#### Incidence of prolonged postoperative ileus

Prolonged postoperative ileus (PPOI) can be diagnosed when at least two of the following symptoms occur after 96 h postoperatively: nausea or vomiting, inability to tolerate any oral diet over the last 24 h, abdominal bloating and distension, or radiological confirmation (32).

## Safety and acupuncture-related adverse events

Acupuncture may cause several adverse reactions or adverse events (33), such as bleeding, pain, dizziness, syncope, needle-sticking, and the like. Therefore, clinical safety will be monitored throughout the trial, and all adverse events will be reported. The patients with adverse reactions may receive relevant treatment, and the possible reasons for adverse events will be discussed to avoid the next occurrence. The number and type of all adverse reactions and events will be summarized during the final safety assessment. The participants will be withdrawn from the study if they experience severe adverse events, and relevant information will be immediately reported to the primary investigator.

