## Outcome measures

### Primary outcome measures

The primary outcomes are the time to first defecation and first flatus, which is regarded as a bowel function indicator. This time is calculated from the end of laparoscopic surgery and will be recorded by nurses with accuracy to the hour.

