## Sample size calculation

Our primary outcome is the time to first defecation. The unpublished experimental data on the effects of AA combined with MA, based on a 2-week prior pilot experiment, were used for the sample size calculation. The time to first defecation is 77.8 ± 15.6 h in the intervention group and 85.1 ± 13.35 h in the control group. We chose the two-sample *t*-test model with a two-tailed test, and the relevant calculating parameters are a significance level of 0.05, a power of 0.80, and an allocation ratio of 1:1. The required number of participants per group is 72. Considering a dropout rate of 10%, the sample size for this trial is 80. Thus, a total of 160 participants will be recruited.

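### Withdrawing patients with severe adverse events from the study, rather than only from treatment, undermines the planned intention-to-treat analysis

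*Protocol article*

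**What the plan says.** Protocol article, Safety and acupuncture-related adverse events: "The participants will be withdrawn from the study if they experience severe adverse events". The rule is mandatory, names the study rather than the study treatment, and is not limited to one arm. Nothing there says whether outcomes are still collected afterwards. The same section promises safety monitoring for the whole trial and a final summary of all events.

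Statistical analysis: "The principle of intention-to-treat (ITT) analysis will be followed in the process of statistical analysis". For gaps in the data: "The last observation carried forward (LOCF) analysis will be applied for missing data in ITT analysis". Then: "Supplementary per-protocol analysis will also be carried out".

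Primary outcome measures: the two primary outcomes, first defecation and first flatus, are each a single time. "This time is calculated from the end of laparoscopic surgery and will be recorded by nurses with accuracy to the hour".

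Table 1 and Secondary outcome measures: hospital stay and PPOI are recorded at discharge, and PPOI is diagnosed from symptoms after 96 h. Adverse events are recorded from Visit 3, before surgery, through to discharge.

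**The concern.** An ITT analysis needs outcomes on everyone randomised. A rule that ends participation because of an event after randomisation produces missing outcomes, and the missingness may be related to the outcome itself. The Background associates ileus with hospital-acquired infection, venous thromboembolism and longer stay, so patients with severe postoperative events may also be slower to recover bowel function.

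The loss may also be unequal. Only the intervention arm is needled, the adverse reactions that the safety section names are needle-related, and participants and acupuncturists are not blinded.

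At stake are both primary event times, hospital stay, PPOI, and safety follow-up in the patients for whom it is most informative.

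**Working it through.** **The plan's own figure.** Inputs from Sample size calculation: "The time to first defecation is 77.8 ± 15.6 h in the intervention group and 85.1 ± 13.35 h in the control group"; "a significance level of 0.05, a power of 0.80, and an allocation ratio of 1:1"; "with a two-tailed test".

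- Planned difference: 85.1 − 77.8 = 7.3 h.
- n per arm = 2 × (1.960 + 0.842)² × SD² / 7.3². With SD = 15.6 in both arms: 2 × 7.849 × 243.36 / 53.29 = 71.7, so 72. This reproduces the stated 72 (the noncentral t gives 72.7, so 73). The root-mean-square SD of 14.52 would give 63.
- Dropout: 72 / 0.90 = 80 per arm, as stated.

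Losing up to 8 patients per arm is therefore already covered for power: 72 per arm gives about 80% at SD 15.6 and about 85% at SD 14.52. The question is bias.

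**What can be imputed.** LOCF needs an earlier measurement of the same variable. Pain, distension and the inflammatory markers have a day-1 value that could be carried to discharge. First defecation and first flatus have none: each is one event time, and before the event there is nothing to carry forward. Hospital stay is likewise a single value. The missing-data rule therefore cannot fill the gap that the withdrawal rule opens.

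**When the loss matters.** The expected time to first defecation is 77.8 to 85.1 h. A severe event before then can remove a primary outcome. A severe event after first defecation leaves that time intact, but still removes hospital stay, PPOI and later safety data.

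**Size of the bias.** Let pI and pC be the proportions withdrawn before first defecation in the intervention and control arms, and h the mean excess time of withdrawn over remaining patients, the same in both arms. An arm's full mean is μ = m + p × h, where m is the mean of those remaining, so m = μ − p × h. The observed difference, control minus intervention, is

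(85.1 − pC × h) − (77.8 − pI × h) = 7.3 + (pI − pC) × h.

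The article gives neither p nor h. The values below are assumptions.

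| pI | pC | h (h) | Bias (h) | Observed difference (h) |
|---|---|---|---|---|
| 5% | 5% | any | 0 | 7.30 |
| 5% | 2% | 15 | +0.45 | 7.75 |
| 5% | 2% | 30 | +0.90 | 8.20 |
| 10% | 5% | 15 | +0.75 | 8.05 |
| 10% | 5% | 30 | +1.50 | 8.80 |
| 10% | 5% | 48 | +2.40 | 9.70 |
| 5% | 10% | 15 | −0.75 | 6.55 |
| 5% | 10% | 30 | −1.50 | 5.80 |
| 5% | 10% | 48 | −2.40 | 4.90 |

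As shares of the planned effect: 0.75 / 7.3 = 10% and 2.4 / 7.3 = 33%. The upper value of h is large: 48 / 15.6 = 3.1 SD.

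**The case against.** **No contradiction in the text.** A reader might infer that the withdrawal rule flatly contradicts ITT. It does not. The safety section never removes these patients from the analysis set, and the statistical section keeps patients with missing data through LOCF. This stands: the rule undermines ITT by withholding outcomes, and the two sections need to be reconciled.

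**An early LOCF value.** A reader might expect LOCF to give withdrawn patients a falsely early time. For the primary outcomes there is no value of any kind to carry forward, so this does not hold.

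**Slowest recovery.** Nothing in the article says that these patients recover bowel function most slowly. The Background reports only a general association of ileus with complications, and a severe needle reaction has no documented link to slow defecation. This stands: outcome-related loss is plausible, not established.

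**A larger bias.** Taking 5 to 10% of one arm with a 24 to 48 h delay gives 0.05 × 24 = 1.2 h to 0.10 × 48 = 4.8 h, or 16 to 66% of 7.3 h. That is the shift in one arm's mean. It equals the bias in the difference only if the other arm loses nobody. Surgical complications occur in both arms and would largely cancel if rates and delays are similar.

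**Condensed article.** The full protocol may say that data collection continues after withdrawal, and the article does promise safety monitoring throughout. So it cannot be asserted that recording does stop. But the objection is to a rule that is stated, not to detail left out, and that rule as worded takes the patient out of the study.

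**Conclusion.** The point holds as a badly fixed rule. Followed as written, it loses outcomes after a post-randomisation event, and the stated missing-data method cannot replace the primary event times. The 10% dropout allowance protects power but not validity.

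The size is unknown because no severe-event rate is given. With equal rates and equal delay, the bias in the difference is zero. With 10% versus 5% withdrawn before first defecation and an excess delay of 15 to 48 h in both arms, it is about 0.75 to 2.4 h, or 10 to 33% of the planned effect. It exaggerates the benefit if the intervention arm loses more patients and understates it if the control arm does. If the delay differs between arms, equal rates no longer guarantee cancellation. The documents do not support a claim of a known direction or of a larger effect.

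**What to change.** Reword the safety sentence so that a severe adverse event does not by itself end study follow-up. Unless the patient withdraws consent, a right that the Recruitment section already grants, first defecation, first flatus, hospital stay, PPOI and adverse events continue to be recorded to discharge and are analysed in the randomised arm, consistently with the Statistical analysis section. Whether study treatment continues is a separate clinical decision for the investigators, recorded with its date; no clinical rule is proposed here.

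The cost is one sentence, plus continued recording of inpatient outcomes; the event times are already recorded by nurses. The sample size stays at 72 per arm, 80 with dropout. The trial was recruiting when the article was written, and event times lost in the meantime may not be recoverable. The change does not repair LOCF for event times that are missing for other reasons, such as withdrawn consent.
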